### **9.2. Data collection**

The data collected in this study will be analyzed by the Sponsor or its designees. All data will be listed individually by patient. For quantitative parameters, descriptive statistics will include the mean, standard deviation, minimum, median, and maximum. For qualitative parameters, descriptive statistics will include the frequency and percentage.

### 9.3. Endpoints

#### 9.3.1. Primary Efficacy Parameter

The primary endpoint is the one-year survival rate. It is defined as the proportion of patients being alive 12 months after their first administration of the study treatment (ipilimumab).

#### 9.3.2. Secondary Efficacy Parameters

To assess safety and additional efficacy parameters of the ipilimumab treatment.

Secondary endpoints are

- Safety / toxicity according to the CTC Criteria (Version 4.0): All adverse events  $\geq$  Grade 3 according to CTCAE, Version 4.0 criteria, that are definitely, probably, or possibly related to the administration of the investigational agents will be assessed and described using descriptive statistics.
- Overall response rate - irOR (irBOR of irPR or irCR) according to immune-related response Criteria (ir-RC) (see 6.3.4.5), and OR (BOR of PR or CR) according to RECIST (see 6.3.3.3).
- Disease control rate - irDCR (irBOR of irCR or irPR or irSD) according to immune-related response Criteria (ir-RC) (see section 6.3.4.5), and DCR (BOR of PR or CR) according to RECIST (see 6.3.3.3).
- Progression free survival rate at 6 months. PFS is defined as the time from the first study treatment date until documented tumor progression (irPD) date (as defined by immune related response criteria) or date of death, whichever occurs first.

Exploratory endpoints

Pharmacodynamic effects of ipilimumab on Absolute Lymphocyte Count (ALC) and correlation of ALC to anti-tumor activity (ORR) of ipilimumab during induction phase (W12)

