**Secondary Endpoint (s)**

- All adverse events  $\geq$  Grade 3 according to CTCAE, Version 4.0 criteria, that are definitely, probably, or possibly related to the administration of the investigational agents will be assessed.
- Overall response rate (PR+CR) according to immune-related response Criteria (ir-RC) at any time in the study.
- Disease control rate irDCR (rate of CR or PR or SD) according to immune-related response Criteria (ir-RC) at any time in the study.
- Overall response rate (PR+CR) according to RECIST criteria at any time in the study.
- Disease control rate (CR or PR or SD) according to RECIST criteria at any time in the study.
- Progression free survival rate at 6 months, PFS is defined as the time from the first study treatment date until the first documented tumor progression date (as defined by immune related response criteria) or date of death, whichever occurs first.
- Overall survival
- Clinical efficacy parameter (1-year OS, ORR, DCR, PFS at 6 months) according to b-raf mutational status of tumor (b-raf V600E yes versus no), brain metastases, LDH and HLA-A2

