#### **6.4.3. Evaluation of Tumor Response Using RECIST Criteria**

##### **6.4.3.1. Definition of Measurable Lesion Response Using RECIST Criteria**

Measurable lesion will be measured in a dimension using the longest diameter is used. The tumour response will be investigated during every re-staging visit.

Complete response (CR): Disappearance of all lesions and appearance of no new lesions.

Partial response (PR): At least a 30% decrease in the sum of the longest diameter of measurable lesions. No new lesions may occur or individual lesions progress.

Progressive disease (PD): At least a 20% increase in the total of the longest diameters of measurable lesions (as reference to the smallest sum recorded since the treatment started) or the appearance of new lesions.

If the measurable lesion disappears and the progression of a lesion or the appearance of new lesions is observed elsewhere at the same time, this is also documented as a progressive disease.

Stable disease (SD): Neither a partial nor a complete response in the absence of progression.

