**6.4.3.3. Determination of Overall Response Using RECIST Criteria**

Overall Response (OR) is determined as the combination of assessments of *measurable* and *non-measurable* lesions using the following criteria:

| Measurable lesions | Non- measurable lesions | New lesions | Overall response |
|---------------------------|--------------------------------|--------------------|-------------------------|
| CR                 | CR                      | No          | CR               |
| CR                 | SD                      | No          | PR               |
| PR                 | SD                      | No          | PR               |
| SD                 | SD                      | No          | SD               |
| PD                 | any                     | Yes or No   | PD               |
| Any                | PD                      | Yes or No   | PD               |
| Any                | any                     | Yes         | PD               |

Best OR is the best confirmed response designation over the study as a whole, recorded between the date of first dose until the last tumor assessment for the individual patient in the study. The assessment of response at 12 weeks has particular emphasis due to the mechanism of action of ipilimumab inducing immune responses as basis for clinical responses. For the assessment of best OR, all available assessments per patient are considered. CR or PR determinations included in the best OR assessment must be confirmed by a second (confirmatory) evaluation meeting the criteria for response and performed no less than 4 weeks after the criteria for response are first met.

Imaging of the brain by MRT or CT, chest, abdomen and pelvis by CT scan is required at screening (ie, baseline) and at each tumor assessment visit in 12-week intervals, regardless of the location of known metastases. Similar methods of tumor assessment and similar techniques (CT or MRT) must be used to characterize each identified and reported lesion at screening and during subsequent tumor assessments. Imaging-based evaluation is preferred to clinical examination.

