**Best Overall Response**

- Best response during therapy prior to PD

| Target lesion | Non target lesion | OR |
|----------------------|--------------------------|-----------|
| CR                   | CR                       | CR        |
| CR                   | SD / IR                  | PR        |
| PR                   | No PD                    | PR        |
| SD                   | No PD                    | SD        |
| PD                   | –                        | PD        |
| –                    | PD                       | PD        |
| –                    | New lesion               | PD        |
| New lesion           | -                        | PD        |

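### Section 9.3.2 defines the RECIST disease control rate without stable disease, so as written it always equals the RECIST response rate and contradicts the synopsis

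*Protocol*

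**What the plan says.** Section 9.3.2 of the protocol lists the response-based secondary endpoints in two consecutive bullets.

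- RECIST overall response: "OR (BOR of PR or CR) according to RECIST (see 6.3.3.3").
- RECIST disease control: "DCR (BOR of PR or CR) according to RECIST (see 6.3.3.3").
- Immune-related disease control, in the same bullet as the RECIST one: "irDCR (irBOR of irCR or irPR or irSD").

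The synopsis, under Secondary Endpoint(s), separates the two RECIST rates. The response rate is "Overall response rate (PR+CR) according to RECIST criteria at any time in the study" and the disease control rate is "Disease control rate (CR or PR or SD) according to RECIST criteria at any time in the study".

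Section 9.5 lists OR and DCR as two separate proportions, each with an exact Clopper-Pearson 95% interval, and assigns both to the Response-evaluable population. It does not define DCR again.

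On the period over which RECIST best response is taken, section 6.4.3.3 says "Best OR is the best confirmed response designation over the study as a whole", from first dose to the patient's last tumour assessment in the study. Appendix 9 says "Best response during therapy prior to PD".

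**The concern.** A disease control rate differs from a response rate only by counting stable disease. If stable disease is left out, the endpoint named DCR repeats the endpoint named OR and adds no information.

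The protocol therefore holds two incompatible definitions of one named secondary endpoint, one in the synopsis and one in the statistics section. An analysis programmed from section 9 would report the response rate under the label of disease control. An analysis programmed from the synopsis would depart from the protocol's own statistical section. Section 9.5 presents results overall, for three cohorts and for four two-way subgroup splits, so the error would recur in 1 + 3 + (4 × 2) = 12 rows.

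The two best-response windows raise a smaller question of the same kind. Re-induction follows progression and takes place within the study (section 5.2). A response first reached during re-induction would count under section 6.4.3.3 but not under Appendix 9.

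**Working it through.** The protocol states no figure that could be reproduced here, so the check compares definitions and then illustrates the size.

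**Step 1: numerators.** In 9.3.2, OR counts patients with a best response in {CR, PR}. DCR counts patients with a best response in {PR, CR}. The sets are identical.

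**Step 2: denominators.** Section 9.5 names the Response-evaluable population for both. An adjacent sentence there puts every patient with at least one dose in the denominators. Whichever sentence governs, it governs OR and DCR alike.

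**Step 3: consequence.** With N the common denominator:

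- as written in 9.3.2: DCR = (CR + PR)/N = OR, with the same exact interval, for any data;
- as in the synopsis: DCR = (CR + PR + SD)/N;
- difference: SD/N, the proportion whose best response is stable disease.

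**Step 4: does anything restore stable disease?** Section 6.4.3.1 treats RECIST stable disease as a category of its own: "Neither a partial nor a complete response in the absence of progression". The cross-reference in the DCR definition does not help. Current section 6.3 is Stopping Rules and has no part 6.3.3.3 or 6.3.4.5. The matching current sections are 6.4.3.3 (RECIST overall response) and 6.4.4.5 (irBOR). Section 6.4.3.3 defines best overall response and does not define DCR, so following the intended reference leaves the definition uncorrected.

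**Step 5: size, by illustration.** These rates are assumptions. N = 200 is the planned maximum; the Response-evaluable population may be smaller, which would widen the intervals but leave the difference in percentage points unchanged for the same shares. Entries are percentages with exact 95% intervals.

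| Assumed CR+PR | Assumed SD | DCR as in 9.3.2 | DCR as in synopsis |
|---|---|---|---|
| 5 | 10 | 5.0 (2.4–9.0) | 15.0 (10.4–20.7) |
| 5 | 20 | 5.0 (2.4–9.0) | 25.0 (19.2–31.6) |
| 5 | 30 | 5.0 (2.4–9.0) | 35.0 (28.4–42.0) |
| 10 | 10 | 10.0 (6.2–15.0) | 20.0 (14.7–26.2) |
| 10 | 20 | 10.0 (6.2–15.0) | 30.0 (23.7–36.9) |
| 10 | 30 | 10.0 (6.2–15.0) | 40.0 (33.2–47.1) |
| 15 | 10 | 15.0 (10.4–20.7) | 25.0 (19.2–31.6) |
| 15 | 20 | 15.0 (10.4–20.7) | 35.0 (28.4–42.0) |
| 15 | 30 | 15.0 (10.4–20.7) | 45.0 (38.0–52.2) |

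**Step 6: the best-response window.** Three places bear on it. Section 6.4.3.3 uses the study as a whole. The synopsis counts RECIST response and disease control at any time in the study, which agrees with 6.4.3.3. Appendix 9 stops at progression and stands alone. Section 5.2 limits re-induction to patients with a response at week 12, or with stable disease lasting at least 3 months from week 12. Where that earlier status also holds under RECIST, the choice of window cannot change a correctly defined DCR. It can change OR only for a patient who goes from stable disease to progression and then to a confirmed response. Patients who have progressed by RECIST but not by irRC are a further group for whom the window may matter; the documents do not allow that group to be sized.

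**The case against.** The strongest case on the other side is that this is a slip whose meaning is plain. The synopsis states the RECIST definition in full, the irRC definition in the same bullet includes stable disease, and a competent programmer would see that the response-rate bracket was repeated. The endpoint is secondary, section 9.5 calls every analysis other than the primary exploratory, and no test, error rate or sample size depends on it. The Statistics part of the synopsis does not even list the RECIST rates among its proportions. All of this stands and it limits the severity. It does not remove the error: a stated endpoint definition gives the wrong result if followed.

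A reader might infer two stronger things.

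- *That a planned comparison of RECIST with irRC would be distorted.* The protocol plans no such comparison; it lists the two sets of results as separate descriptive outputs. A reader of the report could set DCR beside irDCR informally and be misled, but no stated objective or analysis is compromised.
- *That Appendix 9 gives the correct best-response window and section 6.4.3.3 should be changed to match.* The documents do not support that. The synopsis agrees with 6.4.3.3, and section 6.4.5 argues against letting an early increase in tumour volume end the search for response. It is also tempting to say that 6.4.3.3 admits many responses to later therapy, because unlike irBOR in 6.4.4.5 it has no cut at subsequent treatment. Section 6.1.1 follows patients who stopped for progression and switched treatment only for the date of death, and section 5.6.1 bars other anti-cancer agents during the study, so few such assessments should exist.

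**Conclusion.** The point holds. Section 9.3.2 makes the RECIST disease control rate identical to the RECIST response rate, in contradiction to the synopsis and to the parallel irRC definition. That identity rests on no assumption about the data. The understatement equals the stable-disease share; under the assumed 10% to 30% it is 10 to 30 percentage points. Only those percentages are assumed.

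This is a should-fix. It affects one exploratory secondary endpoint whose intended meaning can be recovered, and it leaves the primary endpoint and sample size as they are.

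The differing best-response windows are a real but secondary inconsistency. The documents support asking for one rule, not a presumption in favour of Appendix 9.

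**What to change.** 1. In section 9.3.2, define the RECIST rate as *DCR (BOR of CR or PR or SD) according to RECIST*, which matches the synopsis.
2. In the same bullets, replace the outdated references 6.3.3.3 and 6.3.4.5 with 6.4.3.3 and 6.4.4.5.
3. Reconcile section 6.4.3.3, Appendix 9 and the synopsis on the RECIST best-response window, and state one window before analysis, saying whether responses first reached after progression count. If the window ending at progression is chosen, the synopsis wording must change as well.

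Items 1 and 2 cost one phrase and a few section numbers. Item 3 needs a decision by the sponsor and a sentence or two wherever the rule appears. None of them needs extra data, patients or assessments.

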#### 9.4. Study population

**Intention to Treat (ITT) = Safety population:** All patients who were enrolled and received at least one dose of ipilimumab.

**Response-evaluable population:** All subjects who were treated with at least one dose of ipilimumab with (i) measurable disease at baseline as determined by the irRC; (ii) histologic diagnosis of malignant melanoma; and (iii) at least one screening (i.e. baseline) and at least one on-study TA.

#### 9.5. Statistical analysis

The primary endpoint, one year survival rate, is based on the ITT population. As a simple rate, it will be calculated as the number of patients being still alive 12 months after their first administration of the study treatment divided by the number of patients having received at least one administration of the study treatment. Only subjects known to be alive at 1 year will be included in the numerator. As a time to event variable, it will be derived from the Kaplan-Meier curve. In this case missing data will be censored at the last contact. See below for further details.

All other analyses will have exploratory character. Results will be presented overall and per cohort/subgroup:

- (1) cutaneous vs uveal vs. mucosal melanoma
- (2) - LDH < 2 UNL versus LDH ≥ 2 UNL
- (3) - status brain mets versus no brain mets in medical history
- (4) - status Braf mutation positive versus. Braf mutation negative
- (5) - HLA-A2 positive versus HLA-A2 negative

Demographic and baseline characteristics will be tabulated for all treated subjects. For categorical variables, summary tabulations of the number and percentage within each category (with a category for missing data) of the parameter will be presented. For continuous variables, the mean, median, standard deviation, minimum and maximum values will be given.

Proportions (Survival rate at 1 year, irOR, irDCR, irPFS at 6 mths, OR and DCR) will be presented with exact (Clopper and Pearson) two-sided 95% CI. irOR, irDCR and irPFS are defined according to the irRC; OR and DCR according to RECIST; The date of origin for the survival rate at one year, and irPFS at 6 months is the date of the first ipilimumab dose. Only subjects known to be progression free at 6 months / alive at 1 year will be included in the respective numerators. Any subject receiving at least one dose of ipilimumab will be included in the denominators. The denominator for the irOS and irPFS analyses will be the ITT population. The denominator for the irOR, and irDCR, OR and DCR will be the Response-evaluable population..

Additional analyses treating survival and PFS as time to event endpoints will be performed i.e.: Kaplan-Meier plots will be produced. These will use the ITT population. Survival will be measured, regardless of any re-induction, from the date of the first on-study ipilimumab dose until date of death. Survival time for subjects, whose date of death is unknown, will be censored at the last date of contact. PFS will be measured, regardless of any re-induction, from the date of the first dose of ipilimumab until the first on-study documented date of progression, as per irRC, or date of death, whichever comes first. PFS time of subjects not known to progress or die, will be censored at the date of the last tumor assessment. Median survival, median PFS, survival rate at 1 year and PFS rate at 6 months, all as derived from the Kaplan-Meier curves, will be presented, together with 95%CI.

Safety will be reported for 70 days (5 half-lives) post last treatment. This period will be considered the on-study safety period. The analysis of safety will be based on the frequency of AEs and their severity for all treated subjects (i.e.: the Safety population). Worst toxicity grades per subject will be tabulated for all AEs. Additionally, drug-related grade 3 or more AEs, immune-related, and serious AEs will be tabulated separately, and listings by subject will be produced for all deaths, all SAEs and all AEs leading to discontinuation of study drug.

All adverse events and serious adverse events recorded during the study will be summarized using descriptive statistics. The incidence of treatment-emergent adverse events (new or worsening from baseline) will be summarized by body system, preferred term, verbatim of adverse event, intensity (based on CTC grades), and relation to the investigational products. Furthermore all adverse events and serious adverse events will be listed.

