## 5 STUDY THERAPY WITH IPILIMUMAB

### 5.1 Induction Treatment

Subjects enrolled after IC will receive ipilimumab according to the protocol of the completed Medarex study MDX010-20 (Hodi et al., NEJM, 2010) as a single agent at a dose of 3mg/kg for 4 times over 10 weeks (1 cycle): The day subjects receive the first dose of protocol ipilimumab therapy will define Day 1. Ipilimumab, 3 mg/kg, day 1 (W1), 22 (W4), 43 (W7), 64 (W10) must be administered intravenously over a 90-minute period every 3 weeks for a total of four doses, as tolerated. This dose demonstrated an overall survival benefit for the first time in treating metastatic melanoma in a controlled randomized clinical study (Hodi et al., NEJM, 2010).

- Electrocardiogram (ECG) examination should be performed during screening and week 12. Patients with an existing myocarditis are excluded from this study. For patients with suspicion of myocarditis e.g. dyspnoea, functional insufficiency etc. ECG examinations have to be performed before each treatment.
- Laboratory evaluations should be performed (refer to section 6.1.1.2) and the results examined before administration of each ipilimumab dose.
- As durable disease stabilization and/or objective tumor response can be seen after early progression before Week 12, it is recommended that, in the absence of dose-limiting toxicities (eg, serious irAEs), all four doses of ipilimumab be administered over the initial 12 weeks even in the setting of apparent clinical progression, providing the subject's performance status remains stable.
- All subjects who enter the induction period, including those who may have discontinued treatment for drug-related AEs should obtain a 12-week, 24-week 36-week and 48 week tumor assessment. Those patients who have evidence of clinical progression during the induction period, should obtain further tumor assessment according to Standard of Care.
- Based on clinical experience in the ongoing and completed melanoma studies, the following recommendations apply for subject management in light of the Week 12 or later tumor assessments:
  - The appearance of new lesions in subjects with other stable or shrinking baseline tumor burden may be experiencing clinical benefit and should continue in follow-up before alternative anti-cancer agents are considered. These subjects can be seen to have continued tumor shrinkage in follow-up scans.

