## **6. STUDY PROCEDURES AND OBSERVATIONS**

### **6.1. Procedures by Visit**

#### **6.1.1. Study Procedures by Visit and Treatment Cycle**

Note that results of all safety laboratory tests (that is, all chemistry and all hematology results) must be obtained and reviewed before ipilimumab administration, as applicable. All laboratory results must be within the established range before ipilimumab is administered. All induction period laboratory samples must be collected within a window of up to 3 days before administration of ipilimumab. Laboratory evaluations using a local laboratory must be performed and the result examined by the investigator before administration of each dose of ipilimumab.

The disease will be assessed at baseline, after 12 weeks and for patients with stable disease or better responses, thereafter every 12 weeks in the absence of PD to a maximum of one year. Response evaluation will be done according to RECIST and immune-related response criteria (1).

All patients who prematurely discontinue treatment due to a drug-related adverse event prior to Week 12 (in the absence of disease progression) will return for all study visits and procedures including Week 12 and, if appropriate, further re-staging assessments until disease progression is observed.

- Subjects who are no longer receiving ipilimumab because of unacceptable toxicity (refractory Grade  $\geq 3$  irAEs) or due to investigator judgment are followed with tumour assessment until ir PD. Efficacy assessments for these subjects during follow-up are as per the standard of care. Date of death is recorded.
- Subjects who discontinue ipilimumab treatments are followed with tumour assessment until ir PD and should be followed until death or the closure of the study (whichever is first).
- Subjects who are no longer receiving ipilimumab because of progression and who have switched to alternative treatment are not followed formally except to record the date of death.

Any patient with documented progression at any scheduled re-staging visit who is not eligible for re-induction treatment will undergo no further re-staging visits and enters the Follow up phase (FU phase).

At the time of closure of the study (LPFV+12 months), it will be ensured that survival status (alive/dead and date) has been collected for each subject for each subject's full follow-up period (i.e: for 1 year from the subject's first treatment dose).

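### The Kaplan-Meier PFS rule carries patients who stop for clinical deterioration without an on-study scan as progression-free until death, or gives them no follow-up if alive, which biases the Kaplan-Meier 6-month and median PFS upward

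*Protocol*

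**What the plan says.** Section 9.5 plans two estimates of PFS at 6 months.

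- **Proportion with exact confidence interval.** "Only subjects known to be progression free at 6 months / alive at 1 year will be included in the respective numerators". On the denominator: "The denominator for the irOS and irPFS analyses will be the ITT population". The ITT population is everyone who received at least one dose (Section 9.4).
- **Kaplan-Meier, also on the ITT population.** PFS runs from first dose "until the first on-study documented date of progression, as per irRC, or date of death, whichever comes first". For the rest, "PFS time of subjects not known to progress or die, will be censored at the date of the last tumor assessment". The results taken from these curves are listed: "Median survival, median PFS, survival rate at 1 year and PFS rate at 6 months, all as derived from the Kaplan-Meier curves, will be presented". The synopsis (Statistics) states the same event and censoring rule.

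Other sections determine who gets scanned.

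- Scheduled tumour assessments are at baseline, week 12 and every 12 weeks after that (Section 6.1.1). The baseline images may be up to 6 weeks old at first dose (Section 6.1.1.1).
- Clinical deterioration is in itself a reason to stop treatment, and the reason for stopping is recorded (Section 5.5.3).
- Section 5.1 says: "Those patients who have evidence of clinical progression during the induction period, should obtain further tumor assessment according to Standard of Care".
- Under Section 6.1.1, patients who stopped because of progression and "who have switched to alternative treatment are not followed formally except to record the date of death".
- Survival status is collected for one year from first dose (Section 6.1.1.5).

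**The concern.** The Kaplan-Meier event needs a measured irRC progression or a death. Someone who fails clinically before week 12 and is not imaged afterwards has neither until death. The rule has no clause for clinical progression, for new therapy, or for a patient with no on-study scan.

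This censoring is informative, because the patients concerned are among the earliest failures. They either stay on the curve as progression-free or drop out of it at the start. Median PFS has no other estimate in the plan, so nothing else in the report would show the effect on it. Results are also given by cohort. With about 20 uveal and 20 mucosal patients assumed in Section 9.1, one such patient is already 5% of a cohort.

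**Working it through.** **The plan's own figures.** The protocol states no PFS rate, median or precision. Its whole-cohort precision figure concerns 1-year survival with 200 patients (95% CI 0.43 to 0.57). It reproduces: 0.5 ± 1.96 × √(0.25/200) = 0.431 to 0.569. It is not affected by this point.

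**Two patients under the rules as written.** Both stop in week 8 for clinical deterioration and have no scan after baseline.

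| | Kaplan-Meier PFS | 6-month proportion |
|---|---|---|
| A: dies in month 9 | event at 9 months, so progression-free at 6 months | not known to be progression-free: failure |
| B: alive at 12 months | last assessment is the baseline scan, on or before first dose: no time at risk | not known to be progression-free: failure |

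A patient of this kind who dies before month 6 is an event by month 6 under either approach. That patient does not inflate the 6-month rate, but the event is dated too late, which can move the median.

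**Size.** Let q be the share with clinical failure and no on-study scan, S0 the 6-month PFS in all others, and d6 and d12 the fractions of the q group dead by months 6 and 12. Assume the others are not censored before month 6.

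- Clinical failure counted as an event: S(6) = (1 − q) × S0.
- Rule as written: S(6) = [(1 − q) × S0 + q × (d12 − d6)] / [1 − q × (1 − d12)].

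The second numerator is never smaller than (1 − q) × S0 and its denominator never exceeds 1. The written rule therefore never gives the lower value.

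**Assumed inputs, none of them in the protocol.** S0 = 0.30; clinical failure uniform over weeks 3 to 12 (0.69 to 2.76 months); exponential survival afterwards with median m of 3 or 6 months. Then d(t) is the average of 1 − 2^(−(t − u)/m) over u from 0.69 to 2.76:

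- m = 3: d6 = 0.624, d12 = 0.906
- m = 6: d6 = 0.388, d12 = 0.694

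For q = 10%:

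- m = 3: (0.270 + 0.1 × 0.282) / (1 − 0.1 × 0.094) = 0.2982 / 0.9906 = 30.1%
- m = 6: (0.270 + 0.1 × 0.306) / (1 − 0.1 × 0.306) = 0.3006 / 0.9694 = 31.0%

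| q | Clinical failure as event | Rule as written | Excess (points) |
|---|---|---|---|
| 10% | 27% | 30 to 31% | 3 to 4 |
| 20% | 24% | 30 to 32% | 6 to 8 |
| 30% | 21% | 30 to 33% | 9 to 12 |

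**A second set of assumptions.** Clinical failure at week 8; median survival afterwards 2, 4 or 6 months; the others progress at the week 12, 24, 36 and 48 scans with probabilities 0.45, 0.25, 0.20 and 0.15, so S0 = 0.55 × 0.75 ≈ 0.41. The excess is 2 to 4 points at q = 10%, 4 to 9 at 20% and 7 to 13 at 30%. A simulated Kaplan-Meier curve agreed with the closed form. The simulated median moved from 2.8 months to between 4.5 and 5.5 months. Most of that jump arises because events fall on 12-week scan dates, so it shows direction and should not be taken as a forecast. The fixed-denominator proportion equalled (1 − q) × S0 throughout, an excess of zero.

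**The case against.** Four points can be made for the plan, and each has some force.

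**The conservative figure is already planned.** A reader might infer that the trial's 6-month PFS as such is overstated. The documents do not support that. The proportion in Section 9.5 keeps these patients in the denominator and out of the numerator. The point is confined to the Kaplan-Meier 6-month rate and the median, which Section 9.5 presents as additional analyses.

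**The group may be small.** It would be too strong to say that clinical progressors simply stop being scanned. Section 5.1 says they "should obtain further tumor assessment according to Standard of Care", which is a request to image. Section 6.1.1 follows patients who discontinue with tumour assessments until irPD, and Section 6.1.1.3 asks for scans every 12 weeks until progression. Death-only follow-up applies to those who both progressed and switched therapy. These provisions shrink the group but do not guarantee a scan. The response-evaluable population in Section 9.4 requires an on-study assessment, which suggests that some treated patients were expected to have none.

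**irRC was chosen deliberately.** Section 5.1 notes that stabilisation or response can follow apparent progression before week 12. Some clinical failures may therefore not be true progressions, and the lower column in the tables is a different event definition, not a known truth. This stands. It is a reason not to replace the irRC endpoint, but it does not justify presenting the irRC-only curve alone.

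**The date convention for a patient with no on-study scan could sit in a SAP.** That is fair for the convention alone, and censoring at first dose would add no follow-up either. The event and censoring rule, however, is fixed in the protocol.

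**Conclusion.** The point holds for the Kaplan-Meier estimates. As written, the rule makes the Kaplan-Meier 6-month rate and the median PFS upper estimates whenever some patients fail clinically and are never rescanned. The two planned 6-month figures will differ because of those same patients.

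The direction follows from the rule, taking clinical failure as the comparison event. The size does not follow from the documents: it rests on an assumed unscanned share, an assumed base rate of 30% and assumed survival after clinical failure. On those assumptions it is about 3 to 4 points at a 10% share and 6 to 8 at 20%. The 30% row shows the trend only, since nothing in the protocol suggests a share that high. For scale, with 200 patients and a rate of 30% the 95% half-width is 1.96 × √(0.3 × 0.7/200) ≈ 6 points. The bias is thus below sampling error at a 10% share and about equal to it or above at 20%.

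A reader might also infer that the trial's main conclusion is at risk. It is not. The primary endpoint is 1-year survival, and everything else in Section 9.5 is labelled exploratory.

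**What to change.** In Section 9.5 and the synopsis, keep the irRC-only Kaplan-Meier PFS and add a second Kaplan-Meier analysis. In it, where no irPD was documented earlier, discontinuation for clinical progression or deterioration, or the start of non-study anti-cancer therapy, is an event on that date. Report the two curves side by side, with the number of treated patients who have no on-study scan, overall and by cohort. State that the irRC-only Kaplan-Meier median and 6-month rate are to be read as upper estimates.

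The cost is mainly wording, since Section 5.5.3 already records the reason for stopping. The start date of subsequent therapy must be captured. Section 6.4.4.5 already needs it, because irBOR uses assessments before subsequent therapy, but the follow-up phase lists only survival status, so the case report form should be checked. The drawback is that a few patients who switch without true progression will count as failures in the added analysis. No patient's treatment or visit schedule changes.
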